## Abstract

**Background:**

Haemorrhoids are common and can significantly impact the personal and working lives of individuals. Those with more severe symptoms and those not responding to conservative management may require surgery. Current surgical techniques are associated with a degree of postoperative discomfort which may delay return to normal activity. Recurrence is lower in more radical procedures but resulting pain is higher. Radiofrequency ablation (RFA) is a new technique that is gaining popularity and has several hypothesised benefits, including reduced pain and recurrence. However, available evidence is limited. A recent overview from the National Institute for Health and Clinical Excellence recommended more research, in the form of randomised controlled trials, be carried out before further investment is made by national health services. Our aim is to assess whether RFA is at least as good in terms of recurrence as existing surgical interventions, but superior in terms of pain, for patients with symptomatic grade II and III haemorrhoids.

**Methods:**

The RadiO fRequency ablatION for haemorrhoids (ORION) trial will be a pragmatic multicentre patient/assessor-blind parallel group-controlled trial with economic evaluation. The target sample size is 376 participants (188 per arm) and is based on two co-primary endpoints: (i) a non-inferiority design for recurrence and (ii) superiority design for pain at seven days. Participants with grade II or III haemorrhoids will be recruited in 16 National Health Service hospitals and randomised (1:1) to either RFA or surgeon’s choice of surgery.

**Conclusions:**

Results will inform future practice for the treatment of grade II–III haemorrhoids and provide evidence for national health services on future investments in RFA.

**Trial registration:**

ISRCTN14474552.

## Introduction

Haemorrhoids result from pathological changes to the vascular tissue that forms the anal canal and cause symptoms including discomfort and bleeding, frequently resulting in patients presenting for review in surgical clinics. As many as 1 in 3 individuals are affected [1], with over 20,000 operations carried out each year in England alone [2]. Haemorrhoids can cause significant disruption to the personal and working lives of the affected population, as treatment often involves frequent hospital visits and extended recovery periods.

Treatment is determined by the extent of the symptoms and the degree of prolapse, and expert opinion and current guidelines both promote a tailored approach to treatment selection [3]. A number of surgical interventions are currently available to patients, including haemorrhoidal artery ligation (HAL), stapled haemorrhoidopexy, and techniques for surgical excision, all of which are routinely performed under regional or general anaesthetic [3]. Post-surgery discomfort is associated with all treatment options. In the longer term, recurrence of symptoms is not uncommon. Most recent evidence suggests that open haemorrhoidectomy is the most painful in the short term, but it is the least expensive, and better quality of life is observed in the long-term [4–6]. At present, all three interventions are recommended for use [3].

An alternative treatment might be radiofrequency ablation (RFA), which has emerged as an option for patients with haemorrhoids [7]. Like the surgical interventions discussed, RFA is generally suitable for those where office procedures such as Rubber Band Ligation (RBL) have been unsuccessful, or for those with more significant prolapse which is unlikely to respond to less radical intervention [7]. Compared to excisional treatments, RFA has been proposed as a faster procedure with more rapid recovery as it does not excise tissue or generate excess heat. Together, these features of RFA have led to its increasing popularity. However, existing evidence is limited to small cohort studies in specialist settings [8, 9], and pertinently, the promising longer term effects have not been rigorously tested in a randomised comparison.

Evidence on RFA was summarised in a National Institute for Health and Care Excellence (NICE) overview [7]. This concluded that the quantity and quality of existing evidence on the safety and efficacy of RFA for haemorrhoids is inadequate and that further randomized controlled trials (RCTs) are encouraged with outcomes including pain, secondary haemorrhage, recurrence rate, the need for repeat procedures and quality of life measurements.

If more rigorous evidence can demonstrate that RFA can achieve outcomes at least as effective as current recommended interventions, whilst showing superior outcomes for the patient in terms of reduced inconvenience and more rapid recovery, then RFA can be legitimately incorporated in the treatment algorithm for haemorrhoids, particularly if more cost-effective. However, if the RFA procedure does not meet these criteria, health services will be able to disinvest.

The primary aim of this trial is to assess whether radiofrequency ablation is at least as good as existing methods for treating haemorrhoids in terms of recurrence but superior in terms of postoperative pain.

## Materials and methods

This protocol has been prepared with reference to the Standard Protocol Items: Recommendations for Interventional Trials (SPIRIT) guidelines. The trial will be a pragmatic multicentre patient/assessor blind parallel group individual participant randomised (1:1 allocation) controlled trial with economic evaluation. The trial will take place in clinical sites in the UK which offer elective surgery for haemorrhoids.

### Eligibility criteria

Participants will be adults aged 18 years or over with symptomatic second- or third-degree haemorrhoids [10]. Potential participants will have failed conservative managements (diet and lifestyle changes) and requested further intervention, or have either failed one rubber band ligation (RBL) procedure, have haemorrhoids considered inappropriate for RBL treatment, or their surgeon considers the haemorrhoids suitable for surgical intervention.

Patients with certain pre-existing medical conditions will be excluded, including known perianal sepsis, inflammatory bowel disease, anal or colorectal malignancy, pre-existing sphincter injury. In addition, patients with an immunodeficiency (human immunodeficiency virus or other medical cause), unable to have general or spinal anaesthetic, or currently taking warfarin, direct oral anticoagulants that cannot be safely stopped prior to surgery or with any other hypocoagulability condition that may increase the risk of bleeding, or have a pacemaker, will be excluded. Pregnant women and patients who are unable to give full informed consent (due to mental capacity barriers) will also be excluded.

### Intervention

The intervention is RFA (using the Rafaelo^®^ device, Modern Aesthetic Solutions Ltd, UK). The control arm is surgeon choice of surgery, which could be one of stapled haemorrhoidopexy, HAL or haemorrhoidectomy (consistent with international guidelines [3]). ORION will be a pragmatic trial; all procedures will be conducted as per standard care at individual hospitals. RFA has NICE approval where there are arrangements for clinical governance, consent, and audit or research [7].

### Patients randomised to RFA

RFA is available to the UK National Health Service (NHS) through the Rafaelo^®^ device. A special needle probe is inserted into the haemorrhoidal cushion, through which radiofrequency energy is applied, aiming to restrict its blood supply causing it to necrose autoamputate, relieving the patient of their symptoms. In the UK, RFA is generally performed under general anaesthesia with the patient positioned in lithotomy. It can be performed under local anaesthetic. A proctoscope (F care systems, Antwerpen, Belgium) with a simple vent on one side, through which a single haemorrhoidal tissue protrudes, is placed in the anal canal. At a level approximately 5 mm above the dentate line, the submucosa of haemorrhoidal tissue is infiltrated with approximately 1 ml of bupivacaine 0.25%. In addition to achieving local anaesthesia, this step creates a fluid barrier to prevent the transmission of heat to the internal anal sphincter muscle. The Rafaelo^®^ device and associated HPR45i probe (F care systems, Antwerpen, Belgium) are used to deploy RFA energy of 4 MHz frequency to the haemorrhoidal tissue. The tip of the probe is inserted fully into the haemorrhoid tissue approximately to a depth of 5–10 mm, at an approximately 30° angle to the tissue surface. The haemorrhoidal tissue is tilted away from the submucosal layer. The application of RFA is continued until the tissue exhibits whitish discolouration, after which the energy is applied to the external surface of the haemorrhoidal tissue to optimize tissue desiccation. An optimum of 3000 J with a power setting of 25 W is applied to an individual haemorrhoidal tissue at one time. A cold saline-soaked tonsillar swab is immediately applied to the surface of the haemorrhoidal tissue. Any bleeding is controlled by inducing coagulation using the radiofrequency probe [8].

All surgeons involved in the study will have completed training and will have experience of at least five procedures prior to recruiting to the study.

Participants will receive standard supportive care for a surgical intervention, as per local procedures. This will usually be in the form of available clinical contact for any concerns as well as access to clinicians responsible for the participant care if appropriate.

### Patients randomised to surgeon’s choice of other procedures currently available in the UK

The alternative therapies vary, and often depends on the preference of the surgeon. Stapled haemorrhoidopexy, HAL and haemorrhoidectomy are all available in the UK NHS and appropriate conventional therapies according to international guidelines [3]. The control arm will therefore comprise the ‘surgeon’s choice’ of operation based on one of these three options.

### Outcomes

The co-primary outcome measures are recurrence at 12-months post-procedure, defined as per the HubBLe trial [6], and average Numeric Pain Rating Scale (NPRS) at 7 days post-procedure [11].

Secondary outcome measures include:NPRS (1, and 21 days 6 weeks and 1 year post-procedure)Number of days of work lost (measured by research nurse at 6 weeks post-procedure)Persistence of haemorrhoidal symptoms at 6 weeks post-procedureHaemorrhoid severity score [12]EuroQol 5 Dimension 5 Level (EQ-5D-5L)[13] (days 1, 7 and 21, 6 weeks, 1 year post-procedure)Self-report, 7-item Vaizey incontinence score (6 weeks, 1 year post-procedure) [14]Health and social care resource use questionnaire (6 weeks, 1 year post-procedure)Complications (see Table 1)Cost

**Table 1 Tab1:**
[figure not shown]
Use of assessment instruments during the trial

Outcome data (Table 1) will be collected by research nurses, consultants and specialist nurses, either in-person at Standard Operating Procedures (SOPC) (baseline data, 6 weeks follow-up if the usual clinic is face-to-face) or by telephone questionnaires (day 1, 7, 21 and 12 months, and at 6-weeks if the usual clinic format is by telephone) or by completed postal questionnaire (12 months postoperatively). In addition, the 12-month data on recurrence, complications, resource use and need for further treatment will be supplemented by hospital/GP note review. In the instance of disparity of responses between the consultant/hospital notes, serious adverse events (SAE) reports, consultant and general practitioner (GP) records and the participant, the chief investigator will act as the ultimate arbitrator. In the scenario of no response from the patient with regard to recurrence but with another procedure to treat haemorrhoids in their medical notes, this will be recorded as a recurrence. Measuring recurrence based on SAEs will be treated on a case-by-case basis. For example, bleeding within 2–3 days of the procedure which subsided would not be categorized as a recurrence, but uncontrolled episodes later would.

Participant study data will be recorded on study-specific case report forms (CRFs) and patient questionnaires and then entered onto a remote web-based data capture system, transferring data to Sheffield Clinical Trials Research Unit (CTRU) for analysis. All aspects of data management will be provided by the Sheffield CTRU in accordance with their own standard operating procedures.

### Participant recruitment and timeline

Patients will be recruited from 16 UK NHS hospitals over a 14-month recruitment period. The patients care team will conduct an initial case note review for eligibility. Potential participants will receive an approved Participant Information Sheet and given the opportunity to ask questions from both the surgical and research team at their hospital before enrollment into the trial. Participants will be approached either by the local Principal Investigator (PI) or a delegated team member with the appropriate Good Clinical Practice (GCP) training. Participants will give written consent either by remote postal consent, or face to face at surgical outpatient’s clinics. Reasons for non-consent will be recorded where possible and monitored by the study team.

After consent participants will be individually randomised in equal proportions at all centres using a remote, web-based randomisation system.*Group A*: RFA using the Rafaelo^®^ device or*Group B*: Surgeons’ choice of other procedures currently available in the UK NHS.

Baseline data will be collected on the day of surgery or up to 4 weeks before surgery. Details of the procedure will be recorded during or shortly after the surgery. Following the procedure data will be collected to establish scores of pain, as well as which patients have further treatment for recurrent symptoms or complications. This will be achieved using follow-up telephone questionnaires at 1, 7 and 21 days; at a clinic visit around 6 weeks after the intervention; and by interrogating hospital records, asking the patients consultant and writing to the patients GP at the 12-month follow-up. A summary of the participant involvement can be found in Fig. 1.

**Fig. 1 Fig1:**
[figure not shown]
Participant study flow diagram for visits and data collection. *EQ-5D-5L* EuroQol 5 Dimension 5 Level

A patient can withdraw from the trial at any point without giving reasons. Data collected up to the point of withdrawal will be retained. The date of withdrawal will be recorded on the case report form and the web-based data capture system. A summary of data collection can be found in Table 1.

### Sample size

The target sample size is 376 participants (188 per arm) and is based on two co-primary endpoints: (i) a non-inferiority design for recurrence and (ii) superiority design for pain at 7 days. Previous research has demonstrated RFA is associated with a recurrence rate of 4% to 15%, compared with 15% for haemorrhoidectomy and 25–30% for HAL. Our patient panel members have advised us that RFA would be acceptable if we could rule out a 10% increase in recurrence, which we have used as our non-inferiority limit, accompanied by a reduction in pain. The trial will recruit 376 participants (188 per arm), which provides 90% power to declare non-inferiority based on a 15% drop out, an Intraclass Correlation Coefficient (ICC) of 1% among 16 surgeons, a one-year recurrence rate of 15% for intervention and 20% for usual care, a non-inferiority limit of 10% and a one-sided 2.5% significance level. These assumptions are heavily based on our previous HubBLe trial which found a 12% drop-out in the HAL surgery arm and a zero ICC for 12-month recurrence [6]. A sample size of 376 ensures a 90% power to detect a minimal clinical importance difference (MCID) of 0.6 points (1/3rd of a standard deviation) in Numeric Pain Rating Scale-reported pain at 7 days at the two-sided 5% level assuming 5% missing data, a correlation of 0.5 between baseline and follow up and an ICC of 1%. No adjustment for multiple testing is necessary since RFA will need to demonstrate significance on both endpoints.

### Assignment of intervention

A web-based randomisation system will generate random assignment with stratification by hospital. Research staff at hospitals will enrol participants on the randomisation system. Outcome assessors, statistician and participants will be blinded to allocation. In the event a patient or clinician needs to reveal allocation this is accessible through the unblinding procedure on the randomisation system.

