### Statistical and health economic analysis

Analyses of recurrence will be performed using generalised estimating equations (GEE) using the binomial family and the logit link treatment arm and grade of haemorrhoid as fixed effects, with surgeon being incorporated as a clustering term. The difference in proportions and its associated CI will be derived using the delta method [15]. Pain scores at day seven will be analysed using GEE with an identity link; the fixed effect covariates will be treatment arm, grade of haemorrhoid and pre-procedure pain rating, with surgeon again incorporated as a clustering term. Secondary endpoints will be analysed analogously. Unadjusted analysis (difference between arm and 95% CIs) will be reported alongside adjusted analysis.

Safety will be assessed by (i) post-surgical complications and (ii) postsurgical complications leading to SAE, both of which will be summarised for each arm by the number of participants experiencing (a) each complication type at least once and (b) any complication at least once.

The primary analysis will use the Intention to Treat (mITT) population (we do not follow-up participants who withdraw before surgery). For the primary outcomes only, Per Protocol (PP) and As Treated (AT) populations will be considered for sensitivity analysis. There is no a priori defined sensitivity analysis for secondary outcomes.

We will use an interaction statistical test between intervention arm and subgroups to directly examine the strength of evidence for the between arm difference varying between subgroups for the primary outcomes. Age and grade of haemorrhoid will be the only a priori defined sub-groups to be considered for interaction test. Sub-group analysis will be performed regardless of the statistical significance on the overall intervention effect.

Case and item missing data will be examined and multiple imputation methods will be used to reduce bias due to any missing responses in the analyses. Where appropriate, modelling methods that generate robust standard errors (SEs) in the presence of missing data will be considered.

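### Hospital, the only stratification factor, is in neither primary model, and nothing states that surgeon, the clustering term, coincides with it

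*Protocol article*

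**What the plan says.** - **Randomisation** (Assignment of intervention): "A web-based randomisation system will generate random assignment with stratification by hospital". No other factor is named.
- **Recurrence model** (Statistical and health economic analysis): a logit GEE with "treatment arm and grade of haemorrhoid as fixed effects, with surgeon being incorporated as a clustering term".
- **Day-7 pain model** (same section): an identity-link GEE in which "the fixed effect covariates will be treatment arm, grade of haemorrhoid and pre-procedure pain rating, with surgeon again incorporated as a clustering term".
- **Sites** (Participant recruitment and timeline): "Patients will be recruited from 16 UK NHS hospitals over a 14-month recruitment period".
- **Clusters in the sample size** (Sample size): the recurrence calculation is "based on a 15% drop out, an Intraclass Correlation Coefficient (ICC) of 1% among 16 surgeons".
- **Local practice** (Intervention): "all procedures will be conducted as per standard care at individual hospitals".

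Randomisation follows consent, and procedure details are recorded during or shortly after surgery. The article does not say when the operating surgeon is assigned, how many surgeons each hospital has, or whether a surgeon treats both arms. It does say that all study surgeons will have completed RFA training and at least five procedures.

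**The concern.** Stratified randomisation balances the arms within each hospital. That gains precision only if the analysis uses the same grouping; otherwise differences between hospitals can stay in the standard error although the design has removed them from the treatment comparison. Some hospital differences are to be expected here, because procedures and supportive care follow local practice.

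Surgeon may or may not stand in for hospital. Surgeon-level clustering treats patients of different surgeons in one hospital as independent. If those surgeons also tend to operate on different arms, the hospital effect that two surgeons share is counted as noise in the treatment contrast.

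The stake is power. RFA must succeed on both endpoints, so an inflated standard error would widen the interval set against the 10-point recurrence margin and weaken the pain test. The article lists the terms of both models itself, so this is not detail merely deferred to an analysis plan.

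**Working it through.** **1. The plan's own figure.** Inputs from Sample size: "a one-year recurrence rate of 15% for intervention and 20% for usual care", margin 10 points, one-sided 2.5%, power 90%, dropout 15%, ICC 0.01, 16 surgeons.

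- Unclustered: (1.960 + 1.282)² × (0.15×0.85 + 0.20×0.80) / (0.10 + 0.05)² = 10.51 × 0.2875 / 0.0225 ≈ 134.3, so 135 per arm.
- Evaluable patients per surgeon: 376 × 0.85 / 16 = 19.98. Design effect: 1 + 18.98 × 0.01 = 1.190.
- 135 × 1.190 / 0.85 ≈ 189 per arm, or 378 in total, against 376 stated. Power at 376 is 90.0%.

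For pain, 0.6 points is one third of an SD, so the SD is 1.8 and 190 per arm are needed unadjusted. With 357 evaluable (376 × 0.95), the design effect is 1.213, and 190 × (1 − 0.5²) × 1.213 / 0.95 ≈ 182 per arm. Power at 188 per arm is about 91%.

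Both figures reproduce with 16 surgeons as the only cluster level. The point does not change them.

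**2. Effect of leaving hospital out.** Simulation under no treatment effect: 16 hospitals of 20 (376 × 0.85 ≈ 320), arms balanced within hospital, continuous outcome, working-independence GEE with robust SE, 4,000 runs per setting. The hospital ICCs are assumptions; the article gives only a surgeon ICC of 1%. Entries are two-sided type I error (nominal 5%, Monte Carlo error about 0.7 points).

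| Hospital ICC | One surgeon per hospital | Two surgeons, each treating both arms | A different surgeon for each arm | Hospital as fixed effect |
|---|---|---|---|---|
| 0 | 6.4% | 5.4% | 6.8% | 5.1% |
| 0.01 | 6.8% | 5.5% | 5.2% | 5.7% |
| 0.05 | 6.7% | 5.8% | 2.4% | 5.7% |
| 0.10 | 6.8% | 5.1% | 1.1% | 5.4% |

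The excess in the one-surgeon column is already there at ICC 0. It comes from an uncorrected robust SE on 16 clusters, not from omitting hospital. The 6.8% at ICC 0 in the different-surgeon column is likewise a few-cluster effect, since no hospital effect exists there.

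Reported against actual SE when surgeons differ completely by arm:
- ICC 0.01: 0.1139 / 0.1124 = 1.01
- ICC 0.05: 0.1313 / 0.1091 = 1.20
- ICC 0.10: 0.1501 / 0.1071 = 1.40

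**3. A weaker link between surgeon and arm.** Simulation of the pain endpoint: 16 hospitals with three surgeons each, N = 357, baseline correlation 0.5, one surgeon per hospital taking 80% of RFA cases (assumption), exchangeable GEE, 1,500 runs per setting. The surgeon-clustered SE is overstated by 8–12% at hospital ICCs of 5–10%. Against the model with hospital as a fixed effect:
- ICC 5%: 0.104 / 0.092 = 1.13
- ICC 10%: 0.111 / 0.092 = 1.21

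For the planned effect of 1/3 SD, power is Φ(0.333/SE − 1.96). SE 0.104 gives Φ(1.25) ≈ 89%, 0.111 gives Φ(1.04) ≈ 85%, and 0.092 gives Φ(1.66) ≈ 95%. The simulated values were 90% against 95% (ICC 5%) and 85% against 94% (ICC 10%).

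A smaller run with similar settings (600 trials, 16 hospitals of 22) gave 94.8% against 95.2% at ICC 1%, and 93% against 96% at ICC 5%. If surgeons are unrelated to arm, the SE loss is 0–2% for hospital ICCs of 1–10%.

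**4. Recurrence events.** 376 × 0.85 × (0.15 + 0.20)/2 = 319.6 × 0.175 ≈ 56. That is too few to support 15 hospital dummy variables.

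**The case against.** The strongest reply is that 16 hospitals and 16 surgeons imply one surgeon per site. Surgeon clustering is then hospital clustering and nothing is lost. This may well be what the planners had in mind, and it matches a sample size clustered by surgeon, but the article never states it.

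A second reply is that every study surgeon is trained in RFA, so each can treat both arms, and in that case error is near nominal. That makes separation by arm less likely without excluding it. A third is that the planning ICC is 1%, with zero reported for recurrence in the team's earlier trial. At 1% the effect is negligible. That reply stands, and it limits the size of the point.

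Three stronger readings are tempting, and the article supports none of them:
- **Surgeon is settled only at operation and is therefore a post-randomisation variable.** The article says only that randomisation follows consent and that procedure details are recorded around surgery. Surgeon is also a clustering term and not a covariate, and no bias in the treatment effect has been shown.
- **The standard errors are too large as planned.** This holds only when surgeons differ by arm and hospital effects exceed the planned level.
- **Power is lost on both endpoints.** Only a continuous outcome was simulated, so the loss on recurrence is an analogy.

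**Conclusion.** The mismatch is on the page: the sole stratification factor is absent from two models whose terms the article fixes. Its consequence is conditional and modest. It is nil with one surgeon per hospital and close to nil where surgeons treat both arms.

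If surgeons differ by arm within a hospital, the reported SE is about 1% too large at a hospital ICC of 1%. At ICCs of 5–10% it is about 8–20% or more too large, reaching 40% with complete separation at an ICC of 10%. Those ICCs and surgeon arrangements are assumptions, and the outcome simulated was continuous. The error is in the conservative direction: leaving hospital out does not inflate type I error, and the target of 376 stands. The correction is worth making because it removes the dependence on surgeon arrangements that the article leaves open.

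**What to change.** - **Day-7 pain:** add hospital as a fixed effect in the primary model. In the simulation this held type I error at 5.1–5.7% at every hospital ICC tried.
- **Recurrence:** either use a Mantel-Haenszel risk difference stratified by hospital, or cluster on hospital with a small-sample correction to the robust SE. Do not enter 15 hospital dummies.
- **Sensitivity analysis:** keep the surgeon-clustered models for both endpoints.
- **Clarification:** state how many surgeons operate per hospital, whether each treats both arms, and whether the surgeon is identified before randomisation.

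The cost is analysis wording and slightly more analysis work. Hospital is known for every participant from randomisation. There are two cautions. Clustering on 16 hospitals without a correction is mildly anti-conservative (6.4–6.8% above; about 7–9% in the smaller run with three surgeons per hospital), so the correction is part of that option. A Mantel-Haenszel analysis stratified by hospital alone also drops the planned adjustment for grade, whereas the hospital-clustered GEE keeps it.
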